## Abstract

**Background::**

There are no clinical trials evaluating the efficacy of combined music and Tai Chi therapy for patients with major depression. Therefore, the primary objective of the present study was to evaluate the efficacy of Tai Chi and music therapy on psychological status and quality of life among patients with major depressive disorder in China.

**Methods::**

This work is a part of a comprehensive research project to assess and provide intervention that potentially improves psychological status and quality of life among patients with major depressive disorder. This research project has been received ethical approval from the Medical Research and Ethics Committee in Taizhou Second People's Hospital (no. tzey2020023). After the introductory briefing, the acceptance to take the presession questionnaire implied the participant's consent to participate in the study. Eligible participants are divided into 3 groups according to completely randomized design: combined group (music therapy + Tai Chi), music therapy alone group, and Tai Chi alone group. The analyses will be performed using SPSS 22.0.0 (SPSS Inc, Chicago, IL).

**Results::**

This protocol will provide a reliable theoretical basis for the following research.

**Conclusion::**

The sample came from a single health center. Therefore, the results cannot be generalized for the entire population.

**Trial registration::**

This study protocol was registered in Research Registry (researchregistry6597).

## Introduction

1

Depressive symptoms affect about 35.1% of community-dwelling older persons and 65% of institutionalized older persons. In South-West China, depressive symptoms have been reported in 24.3% of community-dwelling older persons.^[1]^ Many individuals being treated for depression receive medication therapy only. Drug treatment, however, is often limited by lack of efficacy, side effects, and drug–disease interaction that are particularly problematic among frail older persons. It is, therefore, important to develop efficient, convenient, and cost-effective solutions of reducing the burden of depressive symptoms among older persons.^[2–4]^

Recently, depression can effectively be treated through music therapy. In previous music therapy trials for depression, diverse clinical techniques relying on multiple methods have been employed.^[5]^ Music interventions for older adults are based on the notion that music elicits emotional responses and helps to retrieve memories, with recent support from research suggesting that brain regions responsible for processing music, particularly known familiar songs, may be spared even in late-stage dementia. They are offered in individual, group, and community settings.^[6]^

Tai Chi, a form of Chinese Martial Arts in existence for hundreds of years, is increasingly being used in mental health settings. Meta-analytic reviews indicate favorable outcomes on a range of psychological well-being measures including depression and anxiety, with large effect sizes for both conditions.^[7]^ In 1 randomized controlled trial conducted in an Asian elderly population, Tai Chi had a positive effect on reducing depressive symptoms compared with no treatment in older patients with depression.^[8]^ Tai Chi has also been evaluated as a complementary modality to pharmacotherapy for geriatric depression, with combination treatment showing greater reduction in depressive symptoms than pharmacotherapy alone.^[9]^

However, it is still controversial whether combined music and Tai Chi therapy will be more effective than treatment alone for patients with major depression.^[10]^ Based on the separate effectiveness of Tai Chi and music mentioned above, we combined Tai Chi with soft relaxing Chinese folk music to determine whether a synergistic effect would be present in the control of depressive symptoms among community-dwelling persons in China. Therefore, the primary objective of the present study was to evaluate the efficacy of Tai Chi and music therapy on psychological status and quality of life among patients with major depressive disorder in China.

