### Study population

2.2

Participants recruited into the study need to fulfill the following criteria: aged 18 to 70 years; residing in the targeted communities for at least 1 year; mentally adequately alert to complete the intervention as judged by trained researchers; with a GDS score of 11 to 25 (inclusive of 11 and 25), and agreeable to take part in entire intervention process. Participants with the following characteristics are excluded: individuals who are bedridden, or with severe hearing or visual impairment leading to difficulty completing the intervention; those with a stroke or cardiovascular event within the past 6 months and the presence of other conditions which require medical assessments prior to physical exercise; individuals with a GDS score of 26 or greater (severely depressed); those who are receiving medical treatment for depression; those who exercise more than 3 times per week.

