### Random allocation

2.3

Before starting the study, a randomization list is produced using software-generated randomized numbers; the randomization depends on random blocks of 10. Eligible participants are divided into 3 groups according to completely randomized design: combined group (music therapy + Tai Chi), music therapy alone group and Tai Chi alone group (Fig. 1). The program duration is 12 months. Participants are enrolled by the research assistant. After baseline examination, all patients will be given a full explanation of the treatment protocol and will be required to sign a written informed consent for study participation and for the publication of the results. All the data collectors, statistical analysts, as well as result assessors are not aware of grouping assignment (Fig. 1).

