### Statistical analysis

2.6

The analyses will be performed using SPSS 22.0.0 (SPSS Inc, Chicago, IL). Frequencies and descriptive statistics will be used for patients’ demographic presentation, while means and standard deviations will be calculated for the continuous variables and group differences will be analyzed by using Pearson *χ*^2^test for categorical variables. Kolmogorov–Smirnov test will be applied to check the distribution of data. Independent *t* test will be used in case of normally distributed data, whereas Mann–Whitney *U* test for non-normal distributions. *P* < .05 will be considered significant for all analyses.

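### The stated aim of detecting synergy cannot be met with three arms and no neither-therapy arm; the trial can show only whether the combination beats each component

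*Protocol article*

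**What the plan says.** The Introduction (Section 1) makes four statements that bear on this point, and the Discussion (Section 3) repeats all of them:

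- The open question: "it is still controversial whether combined music and Tai Chi therapy will be more effective than treatment alone".
- The premise: "Based on the separate effectiveness of Tai Chi and music mentioned above", which refers to earlier literature and not to an arm of this trial.
- The aim of combining the two therapies: "to determine whether a synergistic effect would be present in the control of depressive symptoms".
- The objective: "the primary objective of the present study was to evaluate the efficacy of Tai Chi and music therapy on psychological status and quality of life". The Abstract (Background) gives the same objective.

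Section 2.3 names the arms: "combined group (music therapy + Tai Chi), music therapy alone group and Tai Chi alone group". The Abstract (Methods) lists the same three groups, and Table 1 has a column for each of them and no other. The heading of Section 2.4 mentions control protocols, but the text describes no group that receives neither therapy.

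Section 2.6 plans two-group comparisons: "Independent *t* test will be used in case of normally distributed data, whereas Mann–Whitney *U* test for non-normal distributions". It names no interaction contrast.

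**The concern.** Synergy means a joint effect larger than the sum of the two separate effects. Measuring it takes four cells: both therapies, each one alone, and neither. The trial randomises three of them, so a stated aim and the stated design contradict each other. An analysis plan could not repair this, because no analysis recovers the mean of a cell that was never randomised.

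What is at stake is the conclusion. If the combination does better than both single therapies, the stated aim invites the reader to take that as evidence of synergy. Purely additive effects produce the same pattern, and so do some sub-additive ones. The same gap rules out any conclusion about efficacy against no treatment, for either therapy or for the combination.

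**Working it through.** **Inputs.** The three arms come from Section 2.3. The article gives no sample size, effect size or arm means, so there is no figure of its own to reproduce. All arm means below are assumptions for illustration.

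**Step 1: what the three arms identify.** Let C, M, T and u be the mean improvements under the combination, music alone, Tai Chi alone and neither. In terms of a baseline, a Tai Chi effect, a music effect and their interaction, the rows of the design are:

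| Arm | Baseline | Tai Chi | Music | Interaction |
|---|---|---|---|---|
| Combined | 1 | 1 | 1 | 1 |
| Music alone | 1 | 0 | 1 | 0 |
| Tai Chi alone | 1 | 1 | 0 | 0 |

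There are four parameters and the rank is 3. The undetermined direction is (1, −1, −1, 1). Raising the baseline by k, lowering each single effect by k and raising the interaction by k leaves all three arm means unchanged: k − k − k + k = 0 for the combined arm, and k − k = 0 for each single arm. Therefore:

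- Estimable: C − M, C − T, T − M.
- Not estimable: the interaction C − M − T + u, and the effects against no therapy T − u, M − u and C − u.

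A fourth row (1, 0, 0, 0) would raise the rank to 4 and make all of these estimable.

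**Step 2: how much is left open.** Assume C = 10, M = 7, T = 7. The interaction is 10 − 7 − 7 + u = u − 4, and each single-therapy effect is 7 − u.

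| u (unseen) | C − M and C − T | Each single effect | Interaction | Reading |
|---|---|---|---|---|
| 0 | 3 | 7 | −4 | sub-additive |
| 2 | 3 | 5 | −2 | sub-additive |
| 4 | 3 | 3 | 0 | additive |
| 6 | 3 | 1 | +2 | synergy |
| 7 | 3 | 0 | +3 | synergy |

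The observable data are the same in every row. They fit a sub-additive, additive or synergistic combination, and a large single-therapy effect or none.

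**Step 3: does beating both components show synergy?** Since C − T = (M − u) + interaction and C − M = (T − u) + interaction, the combination beats both components whenever the interaction exceeds minus the smaller single-therapy effect.

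- Additive: with u = 0 and single effects of 4 and 4, C = 4 + 4 = 8. The interaction is 8 − 4 − 4 + 0 = 0, yet the combination wins by 8 − 4 = 4 over each.
- Sub-additive with a win: the first row of the table, with interaction −4 and a win by 3.
- Sub-additive without a win: u = 0, M = T = 7 and C = 7 give an interaction of −7 and a difference of 0.

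So a win over both components is compatible with zero interaction and with some negative interactions.

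**The case against.** **Synergistic may be loose wording for better than either alone.** The word stands only in one rationale sentence of the Introduction and its repeat in the Discussion. It is absent from the Abstract, the outcomes and Section 2.6, and no synergy test or decision rule is planned. The sentence just before it asks whether the combination is more effective than treatment alone, which two pairwise comparisons can test. This is a fair reading, and it means the randomisation and the pairwise comparisons need no change. But the aim as written builds on the separate effectiveness of the two therapies, which suggests joint against separate effects. If the looser sense was meant, the wording still has to say so.

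**The efficacy objective.** A reader might infer that the trial claims to establish the efficacy of each therapy separately. The text does not settle that. The objective says neither each nor alone, it follows sentences about the combination, and separate effectiveness is taken from earlier studies. It can be read as efficacy of the combination judged against single-therapy comparators. What stands is that the wording is ambiguous, and that efficacy against no treatment is out of reach on either reading.

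**Improvement within arms.** A reader might also infer that improvement from baseline will be presented as efficacy. The document does not support this: Section 2.6 names no paired or change-from-baseline test.

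**Add-on effects.** Combined against music does estimate what Tai Chi adds when music is given, and combined against Tai Chi does the same for music. Each equals the stand-alone effect only if the effects are additive, which is the point in question.

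**Condensed article.** An article may leave detail to a full protocol. Here both the aim and the arms are stated, and they conflict.

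**Conclusion.** The concern holds as a contradiction between a stated aim and the stated design. With the three arms in Section 2.3, the interaction is not estimable, and neither is the effect of either therapy or of the combination against no therapy. This follows from the arms alone and does not depend on sample size or on any assumed value.

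Its size in this trial cannot be given, because the article states no arm means. The range of −4 to +3 for the interaction rests on assumed improvements of 10, 7 and 7 with u between 0 and 7. It shows only that the sign is undetermined.

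The trial is not uninformative: the comparisons of the combination with music alone and with Tai Chi alone are valid randomised contrasts. That the investigators would report a win over each component as synergy is a possible consequence of the wording, not something the article says they will do.

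**What to change.** 1. In the Introduction and the Discussion, replace the synergy aim with: to determine whether Tai Chi plus music is superior to Tai Chi alone and to music alone.
2. In the Abstract (Background), the Introduction and the Discussion, reword the objective, now "evaluate the efficacy of Tai Chi and music therapy on psychological status and quality of life" in the Abstract, so that it names the combination as the treatment under test and the two single therapies as its comparators.
3. State that the permitted conclusion is superiority over each component, with no claim of synergy or of efficacy against no treatment.

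The cost is a narrower claim. No patients, arms or visits are added, and the randomisation is unchanged.

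Only if a synergy claim is essential would a randomised neither-therapy arm be needed, and that would be a different and larger trial. As an illustration under assumed inputs (0.5 SD, two-sided 0.05, 80% power), a pairwise comparison needs 2 × ((1.96 + 0.84)/0.5)² ≈ 63 per arm. An interaction of the same size needs 4 × ((1.96 + 0.84)/0.5)² ≈ 126 per cell. That is 3 × 63 = 189 patients against 4 × 126 = 504.

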## Materials and methods

2

### Ethical approval

2.1

This work is a part of a comprehensive research project to assess and provide intervention that potentially improves psychological status and quality of life among patients with major depressive disorder. This research project has been registered in the research registry (with number: researchregistry6597) and received ethical approval from the Medical Research and Ethics Committee in Taizhou Second People's Hospital (no. tzey2020023). After the introductory briefing, the acceptance to take the presession questionnaire implied the participant's consent to participate in the study.

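### Consent to the study is said to be implied by accepting a questionnaire in two places, and to be written and signed after the baseline examination in a third

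*Protocol article*

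**What the plan says.** The article describes consent in three places.

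- Abstract, Methods: "After the introductory briefing, the acceptance to take the presession questionnaire implied the participant's consent to participate in the study".
- Section 2.1, Ethical approval, in the same paragraph as the ethics approval number: "the acceptance to take the presession questionnaire implied" consent to take part in the study.
- Section 2.3, Random allocation: "After baseline examination, all patients will be given a full explanation of the treatment protocol". The same sentence goes on to say that they "will be required to sign a written informed consent for study participation and for the publication of the results".

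On allocation, section 2.3 says that "Eligible participants are divided into 3 groups according to completely randomized design". This sentence stands before the consent sentence, but nothing in the section says which of the two steps comes first in time. Section 2.2 (Study population) makes willingness to go through the whole intervention an inclusion criterion.

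**The concern.** Two things look wrong. First, the article gives two different acts as the one by which a person joins the trial: accepting a questionnaire after a briefing, and signing a form after a full explanation. Site staff, an ethics committee or a reader cannot tell from the article which of them enrols a participant. Second, the stricter rule puts the explanation and signature after the baseline examination, so a research procedure is carried out before the participant has been fully informed and has signed.

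What is at stake is mainly participant protection. The trial recruits people with depressive symptoms and two of its three arms include physical exercise. There is also a secondary matter of allocation integrity. The arms are visibly different activities. If a person could learn the assigned arm before signing, the decision to sign could depend on the arm.

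**Working it through.** The plan states no figure on this point and no arithmetic applies. The check is a comparison of the passages.

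1. **Do the statements concern the same consent?** If the implied consent covered only the questionnaire and the written consent covered the trial, both could stand. The wording rules this out. Section 2.1 says that "the acceptance to take the presession questionnaire implied the participant's consent to participate in the study", and section 2.3 says that patients "will be required to sign a written informed consent for study participation and for the publication of the results". Both name participation in the study. The form of consent therefore differs (implied against signed) for the same object.

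2. **Is the implied rule an isolated slip?** No. It appears in the abstract and again in section 2.1, in practically identical words.

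3. **When does the written consent come?** Section 2.3 is explicit: "After baseline examination, all patients will be given a full explanation of the treatment protocol and will be required to sign". Baseline examination comes first, then explanation and signature.

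4. **When does the implied consent come?** It follows a briefing and takes effect when the questionnaire is accepted. Neither the abstract nor section 2.1 mentions the baseline examination. This rule lacks a signature and possibly a full explanation, but it does not put an examination before consent. The timing fault in step 3 thus belongs to the written rule alone.

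5. **Where does allocation fall?** The candidate evidence is the following.
   - The allocation sentence precedes the consent sentence in section 2.3. This is order of text and not order in time. The sentence on enrolment by the research assistant also comes after the allocation sentence.
   - The randomization list is produced before the study starts. That says when the list exists, not when a participant is assigned from it.
   - Only eligible participants are allocated, and eligibility includes willingness to undergo the whole intervention (section 2.2). Some agreement therefore comes before allocation, but it need not be the signed consent.
   - Fig. 1, the patient-flow diagram, might settle the order. It is not available in the text reviewed.

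   The order of signature and allocation is therefore not fixed in the text.

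6. **Can a bias be sized?** No. That would need arm-specific refusal after assignment and the outcome gap between those who refuse and those who stay. The article gives neither, nor a number of participants. Any figure would be an invention.

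**The case against.** The strongest reply is that this is a reporting ambiguity and not a procedural fault. An article condenses the full protocol, the project has ethics approval, and the approved consent procedure is not visible here. The three statements might describe one sequence: a briefing with agreement to enter, then baseline, then signed consent before treatment starts.

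Part of this stands. The document cannot show which procedure the committee approved or which was followed. Condensation, however, excuses missing detail and not two conflicting statements of the same rule. The staged reading also does not fit wording in which both consents are for study participation. Even if it is accepted, signature still follows the baseline examination.

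A reader might go further and infer that participants are allocated first and sign later, so that refusals differ by arm and the groups analysed are no longer the groups randomized. The document does not support this. It rests on sentence order in a paragraph that is not written chronologically. The figure that might show the order is not available, and the willingness criterion in section 2.2 makes late refusal less likely, though agreement given before a full explanation can still change after it.

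A reader might also infer that under both rules people are examined before consenting. That is true only of the signed consent in section 2.3.

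**Conclusion.** The point holds in this form: the abstract and section 2.1 contradict section 2.3 on how consent to the study is given, and section 2.3 places full explanation and signature after the baseline examination. Both parts are read directly from the text and need no assumption.

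Refusal after a known assignment is left open. The document neither states it nor excludes it, and its effect has no size that can be derived. It is a reason to state the order of steps, not evidence of bias.

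The point must still be fixed. Its weight comes from participant protection and from the contradiction in the rule that admits people to the trial, and it does not depend on any estimate of bias.

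**What to change.** Reconcile the abstract, section 2.1, section 2.3 and Fig. 1 into one consent rule, consistent with what the ethics committee approved:

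- full explanation and signed written consent come before the research questionnaire and the baseline examination;
- a participant's allocation is released only after consent and baseline are both complete;
- the implied-consent sentence in the abstract and in section 2.1 is removed, or reworded so that it no longer stands as consent to the study.

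The cost is rewording in three places and the figure, an ethics notification, and possibly a change in the order of procedures at entry. The article shows no visit schedule, so the effect on the number of visits cannot be judged from it.

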### Study population

2.2

Participants recruited into the study need to fulfill the following criteria: aged 18 to 70 years; residing in the targeted communities for at least 1 year; mentally adequately alert to complete the intervention as judged by trained researchers; with a GDS score of 11 to 25 (inclusive of 11 and 25), and agreeable to take part in entire intervention process. Participants with the following characteristics are excluded: individuals who are bedridden, or with severe hearing or visual impairment leading to difficulty completing the intervention; those with a stroke or cardiovascular event within the past 6 months and the presence of other conditions which require medical assessments prior to physical exercise; individuals with a GDS score of 26 or greater (severely depressed); those who are receiving medical treatment for depression; those who exercise more than 3 times per week.

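### The objective is set in patients with major depressive disorder, but Section 2.2 enrols on a GDS score of 11 to 25 and neither requires nor establishes that diagnosis

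*Protocol article*

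**What the plan says.** **Target population.** The Abstract (Background) gives the objective as to "evaluate the efficacy of Tai Chi and music therapy on psychological status and quality of life among patients with major depressive disorder". The Introduction repeats it, ending with "psychological status and quality of life among patients with major depressive disorder in China", and the Discussion closes on the same sentence. The Abstract (Methods) and Section 2.1 (Ethical approval) describe the wider project for the same patients. The research question in the Introduction and Discussion is whether "combined music and Tai Chi therapy will be more effective than treatment alone for patients with major depression".

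**A second description.** Immediately before the objective, the Introduction and the Discussion both give the purpose of combining the two therapies as better control of depressive symptoms in people living in the community. That sentence mentions no disorder.

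**Eligibility (Section 2.2, Study population).** Participants must be "aged 18 to 70 years", have lived in the target communities for at least a year, be alert enough to take part in the judgement of trained researchers, be willing to complete the intervention, and present "with a GDS score of 11 to 25 (inclusive of 11 and 25"). The depression-related exclusions are "individuals with a GDS score of 26 or greater (severely depressed") and "those who are receiving medical treatment for depression".

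**The concern.** A trial's conclusion belongs to the population that its entry criteria define. Here the objective names a diagnosed disorder, while entry rests on a range of a symptom score. The two are not the same: a person can score in the range without the disorder, and a person with the disorder can fall outside the range or be excluded for being under treatment.

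What is at stake is whom the result describes. Reported against the stated objective, a difference between the combined arm and a single-therapy arm would be read as evidence about patients with major depressive disorder. The plan gives no means of showing that the participants were such patients. Analysis cannot repair this afterwards, because the screening described would not identify the participants who do have the disorder.

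**Working it through.** No arithmetic applies. The article gives no figure on this point to reproduce, and the point depends on none. The check sets the stated target beside the full list of criteria.

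| Feature | Objective and research question (Abstract; Introduction; Section 2.1; Discussion) | Eligibility (Section 2.2) |
|---|---|---|
| Condition | Major depressive disorder, or major depression | GDS score 11 to 25 |
| How established | Not stated | By the score; no diagnosis, diagnostic criteria or diagnostic interview is listed |
| Severity | No limit stated | GDS 26 or more excluded |
| Treatment status | No limit stated | Those under medical treatment for depression excluded |
| Setting | China | Residents of target communities for at least 1 year |
| Age | No limit stated | 18 to 70 years |

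**Step 1: does any criterion bring in the diagnosis indirectly?** The inclusion items are age, residence, alertness, GDS score and willingness. The only one left to judgement is alertness, which concerns ability to complete the intervention. The exclusions cover mobility and sensory impairment, recent stroke or cardiovascular event and other conditions needing medical assessment before exercise, GDS of 26 or more, current medical treatment for depression, and frequent exercise. None of these establishes major depressive disorder.

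**Step 2: apply the list to four hypothetical people who meet every other criterion.**

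- GDS 11, without the disorder, untreated: eligible.
- GDS 20, with the disorder, untreated: eligible, but not identified as having it.
- GDS 26, with the disorder, untreated: not eligible.
- GDS 20, with the disorder, under medical treatment for depression: not eligible.

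The first case shows that entry does not imply the disorder. The last two show that the disorder does not imply entry. The second shows that those who have it are not distinguished from those who do not.

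**Step 3: is the article consistent about its target?** No. In the Introduction, and again in the Discussion, the symptom-based aim in community residents and the disorder-based objective stand in consecutive sentences. The first is close to Section 2.2; the second is not.

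**Step 4: can the mismatch be sized?** No. The share of people scoring 11 to 25 who have major depressive disorder is not given and cannot be derived from the article.

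**The case against.** The strongest reply is that the article is not uniform in claiming major depressive disorder. Its symptom-based aim is close to what Section 2.2 enrols, some entrants may well have the disorder, and the arms are compared under randomisation whatever label the sample carries. All of this stands. It limits the consequence to attribution of the result and leaves the comparison itself intact. It does not remove the mismatch, because the primary objective is the sentence that names the disorder.

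Condensation in a journal article is not an answer. Section 2.2 introduces its list as what participants need to fulfil, and the difficulty is that this list conflicts with the objective.

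A reader might infer more than the text supports:

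- *That excluding severe and medically treated people is itself an error.* It is an ordinary eligibility choice, stated openly. No sentence says that results will be claimed for those groups. The exclusions matter only as limits that an accurate statement of the population should carry.
- *That the age range contradicts the plan, because the Introduction leans on older people, for example "Tai Chi has also been evaluated as a complementary modality to pharmacotherapy for geriatric depression".* That is background rationale. The objective is not restricted to older people, so 18 to 70 years does not conflict with it, and the point gives no ground for an analysis by age group.
- *That mixed diagnostic status would shrink the differences between arms through natural recovery.* Improvement common to randomised arms cancels in the difference. Shrinkage needs further conditions, such as a floor effect or a smaller treatment effect in transient cases, and the article establishes neither.
- *That the article's own conclusion overclaims.* The Abstract (Conclusion) does not name the disorder and warns only about the single centre. The problem lies in the objective and in the inference that would follow from it.

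**Conclusion.** The concern holds in a limited form. The objective and research question name major depressive disorder or major depression, while Section 2.2 requires only a GDS score of 11 to 25 in untreated community residents aged 18 to 70 and does not ascertain a diagnosis. The article also describes its target in two different ways. Followed as written, the trial would attach its conclusion to a population that it neither requires nor identifies.

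The size is qualitative: an unknown share of participants would lie outside the named population, and the article allows no estimate. Saying that the trial can tell us nothing about anyone with the disorder would go too far, since some participants may have it. What it cannot do is attribute a result to them, because they are not identified. The comparison between arms remains valid for those enrolled.

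This rests on one assumption: that the list in Section 2.2 is the operative set of entry criteria, as the article presents it.

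**What to change.** Reconcile the Abstract (Background and Methods), the Introduction, Section 2.1 and the Discussion with Section 2.2, in one of two ways.

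1. **Restate the population.** Word the objective, the research question and any later conclusion for those actually enrolled: community-dwelling adults aged 18 to 70 with a GDS score of 11 to 25 who are not receiving medical treatment for depression. This also removes the conflict with the symptom-based aim. It is a change of wording that can be made before any result is reported. Its cost is a narrower claim.
2. **Keep the claim on major depressive disorder.** State in Section 2.2 how the diagnosis is established, and limit the claim to the severity and treatment status enrolled. If no diagnosis is currently made, this changes eligibility, needs an amendment and is likely to slow recruitment. The claim is still narrower than the present objective.

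The first option is enough to resolve the point. Neither option requires a change to the severity or treatment exclusions or to the age range.
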